# ABSTRACT

**Introduction:** Little is known about the weekly frequency required, dissociated from the total weekly training volume, to promote blood pressure (BP) reduction and improvement in other risk markers for cardiovascular diseases. **Objectives:** To evaluate and compare the effects of a combined exercise program (CT) with different weekly frequencies on BP and other cardiovascular risk factors in middle-aged and elderly individuals with hypertension. **Methods:** Men and women aged 50-80 years will participate in this randomized clinical trial with the medical diagnosis of hypertension. They will perform 12 weeks of CT with the same total weekly volume (120-150 min/week). These participants will differentiate their training exclusively by the number of weekly sessions that will be used to perform this weekly volume, one group performing 2 weekly sessions (CT2) and the other group 4 weekly sessions (CT4). Before the beginning of the study (week 0) and at the end of the intervention period (week 13), participants will perform evaluations regarding BP, glycosylated hemoglobin, endothelial function and levels of physical fitness. **Scientific contribution:** This research project is expected to provide solid evidence on the influence of the number of weekly combined training sessions on the chronic reduction of BP and other cardiovascular risk factors in middle-aged and elderly individuals with hypertension.

**Keywords:** Concurrent training; Physical exercise; Ambulatory blood pressure monitoring; Cardiovascular risk factors

# QUALIFICATION OF THE PROBLEM

The sustained elevation of blood pressure (BP) (i.e., systemic arterial hypertension - HTN) assumes a significant condition after the fourth decade of life, with an elevation in the prevalence[^4^](#_ENREF_4) and incidence[^5^](#_ENREF_5) of SAH with increasing age. Sustained elevation of systolic BP (SBP) or diastolic BP (DBP) of 130 or 80 mmHg, respectively[^6^](#_ENREF_6), is associated with increased cardiovascular risk and mortality[^7^](#_ENREF_7)^,^[^8^](#_ENREF_8)^,^ [^9^](#_ENREF_9). Analysis aggregating cohort studies including one million participants has already shown that the risk of coronary artery disease and stroke rise exponentially from PAS 115 mmHg and PAD 75 mmHg[^10^](#_ENREF_10). Furthermore, increases of 10 mmHg and 5 mmHg in SBP and DBP, respectively, are associated with a 40% increase risk of death by stroke and 30% from other cardiovascular diseases (CVD)[^10^](#_ENREF_10).

On the other hand, the reduction of 20 mmHg in SBP and 10 mmHg in DBP leads to a 50% reduction in the chance of cardiovascular events in middle-aged and elderly individuals[^10^](#_ENREF_10). In the Brazilian population, the prevalence of HTN was determined from cross-sectional studies conducted throughout Brazil and according to the criterion greater than or equal to 140/90 mmHg or the use of antihypertensives, with 28.7% (95%IC: 26.2-31.4%)[^11^](#_ENREF_11) in individuals aged 18 to 90 years and 68.9% (95%IC: 64.1-73.3%)[^12^](#_ENREF_12) in individuals aged 60 years or more.

The recent publication of the new directive on prevention, detection, evaluation and management of high blood pressure has established differentiated criteria for the treatment of SAH[^6^](#_ENREF_6). For individuals with no history of CVD and with an estimated risk of the first cardiovascular event (coronary disease, non-fatal myocardial infarction or fatal or non-fatal stroke) of less than 10%, the values of SBP greater than or equal to 140 mmHg or DBP greater than or equal to 90 mmHg were maintained as the cut-off point for starting drug treatment. However, for individuals with previous cardiovascular event, clinical CVD or estimated risk of event greater than or equal to 10%, it established that SBP of 130 mmHg or higher or mean DBP of 80 mmHg or higher should be treated to prevent recurrent events of CVD[^6^](#_ENREF_6). This guideline maintained the previous positions that physical exercise (PE) should be practiced with the objective of reducing BP, and also defined that adult individuals with SBP between 120-139 mmHg or DBP of 80-89 mmHg and without increased cardiovascular risk should follow the non-pharmacological recommendations as a therapeutic strategy. For individuals with prior CVD or high risk, increased physical activity in an PE program is recommended as the first line of treatment[^6^](#_ENREF_6). Similarly, PE programs have shown positive results in other variables associated with increased risk for CVD, with emphasis on results in glycemic control of individuals at higher risk for developing cardiometabolic diseases[^13^](#_ENREF_13)^,^[^14^](#_ENREF_14). If we consider SAH an important risk factor for the development of type II diabetes mellitus[^15^](#_ENREF_15), another clinical condition quite prevalent in the older adult population, the regular practice of PE should be implemented for different populations that are at higher risk of developing CVD.

Due to the high prevalence and low control rates[^16^](#_ENREF_16)^,^[^17^](#_ENREF_17), SAH is considered one of the main modifiable risk factors and one of the most important public health problems[^18^](#_ENREF_18). In addition to the usual treatment of SAH through the use of medications, changes in lifestyle are able to help prevent and treat this condition. Among these changes, the regular practice of PE has received great attention from the scientific community from its beneficial effects in reducing BP[^19-24^](#_ENREF_19). In addition, PE is considered the best strategy for the development of physical fitness, which is directly related to a series of clinically significant outcomes. Different studies have detected an inverse association between cardiorespiratory capacity (i.e., maximum oxygen consumption - VO2max) and risk of death[^25-27^](#_ENREF_25). A cohort study followed 4,631 veteran men with hypertension, demonstrating that greater cardiorespiratory capacity is associated with lower risk of mortality, even in those individuals with other associated risk factors (i.e., diabetes mellitus, body mass index, among others)[^25^](#_ENREF_25). Another variable that is also inversely associated with the risk of death from cardiovascular disease is muscle strength. In men, high values of muscle strength reduced the risk of death by 60% when compared to men with lower muscle strength[^28^](#_ENREF_28).

Results of different meta-analyses confirm the hypotensive effect from performing aerobic exercise (AE)[^22^](#_ENREF_22), resistance (RE)[^29^](#_ENREF_29) and aerobic+resistance (CE)[^24^](#_ENREF_24) in individuals with hypertension. However, the evidence on the benefits of RE is less consistent than that obtained from AE[^3^](#_ENREF_3)^,^ [^24^](#_ENREF_24), which makes necessary to conduct new clinical trials evaluating the chronic benefits of ND in reducing BP in this population. Although considered a physiological response inherent to aging, significant reductions in muscle function, initially observed at ages of 40 years and more pronounced from 65-70 years[^30^](#_ENREF_30), may have serious consequences. One of the main diseases of the muscle system associated with the aging process is Sarcopenia, characterized by loss of strength and muscle mass that leads to a reduction in the functions of this system, leading to an increased risk of adverse outcomes, physical disability, reduced quality of life and increased mortality[^31^](#_ENREF_31). PE, specifically the REs, has been adopted as the main tool to fight this disease. Besides the classic maximum strength gain from this RE model, another variable that has been receiving a growing interest in investigations on the subject is muscle power, pointed out as an important predictor of functional limitations in the elderly[^32^](#_ENREF_32). Due to the different benefits promoted by AE and RE, strategies that associate these two forms of PE are fundamental and should be better investigated in older individuals with higher risk for developing CVD.

Two main mechanisms are associated to the reduction of AP associated to PE: cardiac output (CO) and peripheral vascular resistance (PVR)[^33-35^](#_ENREF_33). Considering that mean BP (MAP) is the functional product of these two variables[^36^](#_ENREF_36), the decrease of one of them, without the proportional increase of the other, results in lower BP values. A recent review pointed out CO as the most responsive mechanism in young individuals and PVR in elderly individuals[^35^](#_ENREF_35). However, from the scarcity of studies evaluating these mechanisms in different populations, new surveys are needed for a better understanding of these responses. In this sense, the analysis of the vascular system, specifically about endothelium-dependent vasodilation is very little explored and may provide new evidence on the mechanisms related to BP reduction through the practice of PE.

The chronic reduction in BP associated with PE seems to be associated with the sum of the acute effects promoted by the exercise sessions (i.e., post-exercise hypotension - PEH). The magnitude and duration of PEH are directly linked to the studied population, presenting better responses in hypertensive individuals, when compared to those who are normotensive[^37^](#_ENREF_37). However, when comparing men and women with similar characteristics, PEH seems to respond in a similar way after performing the same exercise protocol[^38^](#_ENREF_38). When considering this relationship between the acute response (i.e., PEH) and the chronic effect of PE on blood pressure reduction, it is possible to speculate that the number of weekly sessions can have an important influence on the responses of a PE program. This suggests that a greater number of weekly sessions can be more beneficial in reducing BP, if we consider this sum effect of each session that is performed. However, so far, this issue has not been explored in major clinical trials on the subject. Furthermore, the main recommendations on the optimal dose of exercise suggest performing a total weekly volume in minutes per week[^39^](#_ENREF_39)^,^ [^40^](#_ENREF_40), without properly highlighting the importance of weekly frequency decoupled from the total weekly training volume to promote better results in reducing BP and other risk markers for CVDs.

# OBJECTIVES

### General Objective

To evaluate and compare the effects of a combined exercise program (i.e., resistance and aerobic) with different weekly frequencies on BP and other cardiovascular risk factors in individuals with hypertension.

### Specific Objectives

To evaluate and compare the effects of 12 weeks of combined training with different weekly frequencies on the following outcomes in middle-aged and older individuals with hypertension:

*Primary outcomes*

- Daytime, nighttime and 24-hour systolic and diastolic BP, evaluated through ambulatory BP monitoring (ABPM);

- Glycosylated hemoglobin (HbA1c), evaluated through blood collection using the high performance liquid chromatography method.

*Secondary outcomes*

- Endothelial function, evaluated by ultrasonography.

- Cardiorespiratory fitness, evaluated through an ergoespirometric test of maximum effort.

- Neuromuscular function, evaluated through chair-stand test, isometric handgrip test, vertical jump, medicine ball throw and balance tests;

- Quality of life, evaluated through the questionnaire WHOQOL-BREF.

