The sample will consist of 98 participants (49 in each intervention), who will be included according to the above criteria. The sample size calculation was performed considering a minimum difference of 4 mmHg, and dispersion (standard deviation) of ± 10 mmHg in systolic and diastolic BP. A statistical power of 80% and an alpha error of P<0.05 were adopted.

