## Statistical analysis

Shapiro-Wilk and Levene tests will be used for data normality and variance homogeneity, respectively. If the data present normal and homogeneous distribution, parametric statistics will be used. Transformations will be performed if the data do not present normal distribution to make them parametric. The Generalized Estimating Equations (GEE) and the Bonferroni post-hoc test will be used for the comparison between the moments and groups/ interventions. In addition, statistical analysis by protocol will be performed, in which those who have presented three consecutive absences in training will be excluded from the analysis, as well as those who obtain a frequency lower than 75% during the period of interventions. Statistical analysis by intention to treat will also be performed, in which all randomized participants will be included in the analyses. The level of significance adopted will be α = 0.05 for all analyses. The statistical package SPSS version 22.0 will be used to perform the statistical procedures.

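### Seven unranked primary outcomes, each tested at 0.05 in two unranked analysis sets, leave the primary false-positive rate uncontrolled

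*Protocol*

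**What the plan says.** The protocol's Specific Objectives give two entries under primary outcomes. The first is "Daytime, nighttime and 24-hour systolic and diastolic BP, evaluated through ambulatory BP monitoring (ABPM"; three periods by two pressures make six variables. The second is "Glycosylated hemoglobin (HbA1c), evaluated through blood collection using the high performance liquid chromatography method". That makes seven, with no order and no lead outcome.

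The Statistical analysis section states: "The level of significance adopted will be α = 0.05 for all analyses". It plans two analysis sets: "In addition, statistical analysis by protocol will be performed", and "Statistical analysis by intention to treat will also be performed, in which all randomized participants will be included in the analyses". Neither is called primary or supportive. The one multiplicity device is that "the Bonferroni post-hoc test will be used for the comparison between the moments and groups/ interventions".

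The sample size paragraph, under Participants recruitment, uses a single unsplit alpha of 0.05, "considering a minimum difference of 4 mmHg, and dispersion (standard deviation) of ± 10 mmHg in systolic and diastolic BP". It does not say which ABPM period is meant.

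**The concern.** Seven outcomes and two analysis sets offer up to fourteen between-arm results, each judged at 0.05. The protocol does not say whether one, some or all must be significant for the trial to count as positive. A significant difference in nighttime diastolic BP alone, in the per-protocol set alone, could therefore be reported as a primary result for two against four weekly sessions.

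The choice of set matters in its own right. The per-protocol set drops participants with three consecutive absences or attendance below 75%. That is selection after randomisation, and it may act differently in arms with different numbers of sessions to attend.

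The Bonferroni sentence could be mistaken for protection here. As worded, it adjusts contrasts between moments and groups, that is, within the model for one outcome.

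**Working it through.** **The plan's own figure.** The protocol states no familywise error rate, so there is none to reproduce. Its only related figure is the sample size, used in step 5.

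**Inputs from the protocol.** Seven primary outcomes; 0.05 per test; two analysis sets; ABPM daytime 06:00-22:59 (17 h) and nighttime 23:00-05:59 (7 h); 49 per arm; 4 mmHg; SD 10 mmHg.

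**Assumed, because the protocol does not give them.** Two-sided tests; one between-arm test per outcome and set; day-night correlation 0.5-0.9; systolic-diastolic correlation 0.5-0.9; HbA1c independent of BP; correlation between the two sets' test statistics 0.80-0.95. All null hypotheses are taken as true, and any one significant result counts as positive.

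**Step 1: ceiling for one set.** With independent tests, 1 - 0.95^7 = 0.302. These outcomes cannot be independent, because 24-hour BP is built from daytime and nighttime BP.

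**Step 2: how closely 24-hour BP follows daytime BP.** Take 24-hour BP as (17/24) × day + (7/24) × night, with equal variances and day-night correlation r. Its correlation with daytime BP is

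(17/24 + 7r/24) / √[(17/24)² + (7/24)² + 2(17/24)(7/24)r].

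This is 0.96 at r = 0.5 and 0.99 at r = 0.9. A common correlation of 0.5 among all six BP variables, which would give about 25%, is therefore not realistic either.

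**Step 3: one set, and step 4: either set.** Multivariate normal simulation with that structure gives the probability of at least one |z| > 1.96:

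| Systolic-diastolic r | Day-night r | One set | Either set, between-set r 0.80 / 0.90 / 0.95 |
|---|---|---|---|
| 0.5 | 0.5 | 21% | 31% / 28% / 26% |
| 0.7 | 0.7 | 18% | 27% / 25% / 23% |
| 0.9 | 0.9 | 14% | 22% / 20% / 18% |

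Over the whole grid the range is 14-21% for one set and 18-31% if either set counts. Treating all fourteen tests as independent would give 1 - 0.95^14 = 51%, which is unrealistic because the two sets share participants.

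**Step 5: what splitting alpha would do to power.** The standardised difference is 4 / (10 × √(2/49)) = 1.98.

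- At 0.05/7 = 0.00714 two-sided, the critical value is 2.69. Power is Φ(1.98 - 2.69) = 23.9%, or 22.7% with the t distribution. For 80% power, n per arm = 2 × [10 × (2.690 + 0.842)/4]² = 155.9, so 156.
- At an unsplit 0.05, power is already only Φ(1.98 - 1.96) = 51%, and 80% needs 2 × [10 × (1.960 + 0.842)/4]² = 98.1, so 99 per arm. The planned 49 per arm thus does not follow from the stated inputs as a two-arm comparison. That is a separate sizing question.

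**The case against.** **No trial-level claim is made.** The objectives are to evaluate and compare effects on each listed outcome, and the 0.05 is a level for analyses, not a familywise rate. A reader might infer that the protocol promises a trial-wide 5% and breaks it. It makes no such promise. What stands is that no success rule is fixed, so the error is uncontrolled if any single result is used. A rule requiring all seven to be significant would hold the error at or below 5%, but none is stated.

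**This could be left to a SAP.** The ordering of outcomes and the lead analysis set are often fixed there, and one may exist. That softens the point without removing it. The protocol itself fixes an unranked list of seven and one level for all analyses, and a SAP that split alpha would have to depart from that sentence.

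**The size rests on correlations that nobody has given.** This is right, and it is why ranges are shown. A reader might infer a 30% false-positive rate from the count of seven. For one set that needs independence, which the construction of 24-hour BP rules out. Values near 30% arise only at the top of the either-set range.

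**The sample size is a different matter.** The calculation refers to a difference "in systolic and diastolic BP" and has no HbA1c input. A reader might treat this as part of the error-rate problem, but it concerns power and does not change the false-positive rate.

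**Conclusion.** The concern holds in limited form. The protocol names seven unranked primary outcomes, tests each at 0.05 in two unranked sets, and has no device acting across outcomes or sets. If any one significant primary outcome counts as success, the false-positive rate is roughly 14-21% in one set, about three to four times nominal, and roughly 18-31% if either set counts.

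The structural finding comes directly from the text and is firm. The percentages are conditional on the assumed correlations and on the any-one rule, and should be quoted with both. The matter should be settled before results are known, because it decides what the trial may claim.

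**What to change.** Before unblinded results are seen, amend Specific Objectives and Statistical analysis in one of two ways.

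1. **One primary outcome.** Name a single outcome, in the intention-to-treat set, at two-sided 0.05. 24-hour systolic ABPM at week 13 is one example; the documents do not single it out, and the choice is the sponsor's. Move the other six to secondary, reported with estimates and 95% confidence intervals.
2. **Several primary outcomes in a fixed sequence.** State the order in advance. Test each at 0.05 in the intention-to-treat set and stop confirmatory claims at the first non-significant result.

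Either way, label the per-protocol analysis supportive, and say that the Bonferroni step applies within an outcome only.

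The cost is protocol wording and fewer routes to a positive primary claim. Neither option needs an alpha split. Bonferroni or Holm over all seven would also control the error, but not by wording alone. Bonferroni throughout, and Holm at its first step, test at 0.05/7, where 49 per arm has about 23-24% power for 4 mmHg with SD 10 and about 156 per arm would be needed for 80%. That route reopens the sample size.

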# MATERIAL AND METHODS

# **Study Design**

This is a randomized clinical trial with parallel design in which participants will be allocated to one of two groups: Combined training with two weekly sessions (TC2) and Combined training with four weekly sessions (TC4).

## Participants recruitment

Men and women aged 50-80 will participate in the study with a physician’s diagnosis of hypertension.

Individuals will be eligible for this study if:

a) Accept to participate and sign the informed consent form - TCLE (Suppl 1);

b) Have office blood pressure between 130-179 and 80-110 mmHg for systolic and diastolic blood pressure, respectively, or taking at least one antihypertensive medication;

c) They are clinically able to perform the different training proposed in the study.

Patients who meet the inclusion criteria will be excluded from the study if have:

a) Diseases that limit the performance of physical exercises, such as lung disease, valvular heart disease, renal failure;

b) Underlying cardiovascular disease in the last 24 months such as acute myocardial infarction, angina, stroke or heart failure

c) Diseases that can reduce life expectancy;

d) Regular practitioners of physical activities (i.e., 3 or more sessions per week of moderate or vigorous intensity exercises);

e) BMI ≥39,9 kg/m²;

f) Diabetic proliferative retinopathy.

Participants will be recruited through publicity on social networks and posters placed in the Hospital de Clínicas de Porto Alegre and in nearby establishments. In addition, we will invite individuals registered in databases of previous studies conducted by our research group. Prior to the clinical evaluation of the participants, a brief telephone interview will be conducted in order to identify whether the individuals meet the above criteria and to identify interest in participating in the study. After the telephone contact and the interest manifested, the individuals will perform a clinical evaluation composed of anamnesis, baseline BP measurements, anthropometric evaluation (body mass, height and body mass index), and resting electrocardiogram (ECG) in order to identify eligibility or even cardiovascular diseases that limits the performance of the proposed exercises. In addition, participants will receive a copy of the consent form with the detailed information of the study and those eligible will appear at a pre-established date and time for the other evaluations.

The sample will consist of 98 participants (49 in each intervention), who will be included according to the above criteria. The sample size calculation was performed considering a minimum difference of 4 mmHg, and dispersion (standard deviation) of ± 10 mmHg in systolic and diastolic BP. A statistical power of 80% and an alpha error of P<0.05 were adopted.

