## Training programs

The TC2 and TC4 groups will perform the training with progressive intensity and volume, and will perform the same weekly training overload (i.e., minutes per week, series, repetitions, relative intensity and exercises), but will have this overload divided into different weekly frequencies. The training will last 12 weeks, with a total weekly volume of 120 min in the first weeks (weeks 1-6), progressing to 150 min/week in the last weeks (weeks 7-12). Therefore, the groups will differentiate their training exclusively by the number of weekly sessions that will be used to perform this training, with one group performing 2 weekly sessions and the other group 4 weekly sessions.

The first part of the session will consist of the following RE: push-up, squat, unipodal balance, inverted row, calf raise and crunch. The progression in volume will be performed by increasing the number of sets and repetitions. The intensity of the effort will be adjusted from the range of movement of the exercises, speed of execution, and variations in the number of supports to stabilize the exercises. Individuals must perform 1-4 series of 10-15 repetitions with the load corresponding to 60-70% of 1RM monitored through rating of perceived exertion (RPE), monitored through the CR10 scale. An interval of 90-120 seconds will be adopted between sets and exercises. The second part of the session will consist of AE performed on a treadmill or track and will last 20-50 minutes. The intensity of these sessions will be controlled through the heart rate reserve (HR _reserve_) of the individuals, using intensities between 60-70% of HR _reserve_. In the absence of HR monitors, the stress perception scale corresponding to the above intensities will be used, monitored through the BORG scale with rates of 6-20. In the last session of the week at each 4-week period, after the RE and at the end of each session, information will be recorded regarding the RPE of the participants in the session and the level of enjoyment when conducting the training. It should be noted that the training sessions will always start with the RE, and later on, they will perform the AE, as this seems to be the best order to conduct the training in this population[^41^](#_ENREF_41)^,^ [^42^](#_ENREF_42).

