## Evaluations

Before the study begins (week 0) and at the end of the intervention period (week 13), participants will perform evaluations regarding BP, glycated hemoglobin, endothelial function, fitness level, and quality of life. Divided into 3 visits with 24-72h intervals between visits, the different evaluations aim to verify the possible effects of the different interventions on the outcome variables of the study. A food record will be used to characterize eating behavior and to evaluate a possible interference of eating with training responses. The subjects will be recommended not to change their eating habits during the study period.

In the first visit, after signing the TCLE, an anamnesis will be performed to characterize the sample, collection of anthropometric measurements through measures of height and body mass, performed from a stadiometer and an analog balance scale (brand FILIZOLA, BRAZIL). With these values their body mass indexes (BMI) will be calculated, according to the equation mass (kg)/height(m)². A questionnaire will also be carried out to evaluate the quality of life of the participants (WHOQOL-BREF). Also in this session, BP measurements will be performed (after 20 minutes of rest) followed by a familiarization with the exercises that will be used in strength and muscle power tests and with the mask that will be used in gas collection during the cardiopulmonary test.

In the second visit, new BP measures will be performed and the endothelial function evaluation conducted through flow-mediated dilation analysis. The resting electrocardiogram and blood collection will also be performed for analysis of glycated hemoglobin levels. From this blood collection, a sample will be used for analysis of total cholesterol, HDL-c, LDL-c, VLDL-c, which will serve to characterize the sample. Afterwards, the ambulatory blood pressure monitoring equipment (ABPM) will be placed. After 24h of the second visit, each patient must return to the laboratory to remove the ABPM.

On the third visit, after ABPM removal, the evaluation of strength and muscle power tests will be conducted, as well as the cardiorespiratory and unipodal balance evaluation. First the strength, power and unipodal equilibrium tests will be conducted, and after a 10-minute rest, the cardiopulmonary test will be conducted.

*Blood pressure measurement*

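### Inclusion criterion b) applies the upper office pressure limits of 179/110 mmHg only to untreated candidates; a treated candidate meets it at any pressure

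*Protocol*

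**What the plan says.** The Protocol, section Participants recruitment, lists three inclusion criteria that must all be met, followed by six exclusions. Criterion b) is the only one with a blood pressure figure: "Have office blood pressure between 130-179 and 80-110 mmHg for systolic and diastolic blood pressure, respectively, or taking at least one antihypertensive medication". Criterion c) is a clinical judgement without a figure: "They are clinically able to perform the different training proposed in the study".

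Before entry there is a clinical evaluation with history, blood pressure, anthropometry and a resting ECG, done "in order to identify eligibility or even cardiovascular diseases that limits the performance of the proposed exercises". The exclusions cover diseases that limit exercise, cardiovascular disease in the last 24 months, reduced life expectancy, regular exercise, high BMI and proliferative retinopathy. None of them names a blood pressure.

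The section Evaluations adds further readings before training starts. At visit 1: "Also in this session, BP measurements will be performed (after 20 minutes of rest"). At visit 2: "In the second visit, new BP measures will be performed", and then "Afterwards, the ambulatory blood pressure monitoring equipment (ABPM) will be placed". The monitor comes off before the exercise tests of visit 3. No value is given at which a participant would be deferred.

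**The concern.** Criterion b) does two jobs in one sentence. It establishes that the person has hypertension, and it sets an upper bound on office pressure. Drug treatment is a sensible alternative to the lower limits, because controlled hypertension is still hypertension. That reasoning does not extend to the upper limits, since no ceiling is needed to show that someone is hypertensive. As worded, however, being on one drug waives both ends of the range.

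The consequence is an asymmetry for which the protocol gives no reason: a numeric ceiling for untreated candidates and judgement alone for treated ones, although both go on to the same tests and training. The background section (Qualification of the Problem) itself describes control of hypertension as poor, so a treated candidate with high pressure is foreseeable. What is at stake is consistent entry and patient safety, not the validity of the treatment comparison.

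**Working it through.** The protocol gives no figure to reproduce here: it states neither the share of candidates on drugs nor the distribution of office pressure at screening. The check is one of logic.

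**Inputs** (Participants recruitment, criterion b): systolic range 130 to 179 mmHg, diastolic range 80 to 110 mmHg, drug treatment yes or no.

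**Rule as written:** b) is met if (130 ≤ SBP ≤ 179 and 80 ≤ DBP ≤ 110) or treated.

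**Rule as proposed:** b) is met if (SBP ≥ 130 and DBP ≥ 80) or treated; in addition, everyone must have SBP ≤ 179 and DBP ≤ 110.

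| Candidate | Office BP (mmHg) | As written | As proposed |
| --- | --- | --- | --- |
| Untreated | 150/90 | meets | meets |
| Untreated | 150/75 | fails (DBP below 80) | fails (DBP below 80) |
| Untreated | 182/95 | fails (SBP above 179) | fails (SBP above 179) |
| Untreated | 160/115 | fails (DBP above 110) | fails (DBP above 110) |
| Treated | 125/75 | meets | meets |
| Treated | 182/95 | meets | fails ceiling (SBP above 179) |
| Treated | 150/115 | meets | fails ceiling (DBP above 110) |
| Treated | 200/120 | meets | fails ceiling (both) |

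Two things follow. First, under the present wording no treated candidate can fail b), so the upper limits bind only the untreated. Second, the proposed wording changes the status only of treated candidates above 179 or 110 mmHg.

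The table takes the pressure route to require both the systolic and the diastolic range, which is the plain reading. If either range sufficed, some untreated rows would change, but the treatment route would lift the ceiling just the same.

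**Search for a ceiling elsewhere.** Criterion c) and the six exclusions contain none. Nor do Experimental procedures, Training programs, Evaluations, or Ethical considerations. The guideline reference under blood pressure measurement concerns how to measure, not whom to admit.

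**Size.** The number affected cannot be derived from the document. As an illustration on an assumed share, not a bound: if 0% to 5% of the 98 planned participants were treated and above either limit at screening, that is 0 × 98 = 0 to 0.05 × 98 = 4.9 people.

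**The case against.** The strongest reply is that meeting b) is not the same as being eligible. A treated person at 182/95 mmHg must still satisfy c) and pass all exclusions, and is examined with a pressure reading and an ECG before entry. The exclusions remove several groups for whom raised pressure during exercise matters most: valvular disease, renal failure, recent infarction, angina, stroke or heart failure, and proliferative retinopathy. Two further clinic readings and a 24-hour recording precede the first maximal test, a physician attends that test, and training is stopped on symptoms, with nursing and emergency backup. All of this stands. A reader might infer from the wording of b) that treated people with severe hypertension are simply admitted; the document does not support that. It shows only that no stated number stops them.

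It can also be said that 179/110 need not be a safety limit. Criterion b) may just define hypertension, and an untreated person above the range may be left out because drug treatment has to come first. That too stands in part: the protocol states no purpose, so reading the ceiling as a limit on severity or risk is an inference. But neither explanation is written down, and the safeguards listed rest on judgement where the sponsor has already chosen a number for the other group.

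A reader might also treat the scheduled maximal tests and training sessions as a measure of added risk. They are every participant's ordinary schedule and are no evidence of excess harm.

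**Conclusion.** The point holds as a wording fault in one eligibility criterion: the upper office pressure limits bind untreated candidates only, and nothing else in the protocol sets a limit for treated ones. For a treated candidate with markedly raised pressure, entry rests on clinical judgement under c), the exclusions and the screening evaluation.

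The literal logic is certain. The intended purpose of 179/110 is inferred, and the number affected is unknown and probably small. A reader might go on to infer a biased comparison between two and four weekly sessions. The document gives no ground for this: eligibility is settled before randomisation and the same rule applies to both arms. No estimate, sample size or analysis changes. This is a cheap improvement worth making for patient safety, not a flaw that threatens the trial's result.

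**What to change.** Separate the two jobs of criterion b):

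- Criterion b): *office SBP ≥130 mmHg and DBP ≥80 mmHg, or current use of one or more antihypertensive drugs.*
- New criterion: *every candidate, treated or untreated, must have office SBP ≤179 mmHg and DBP ≤110 mmHg at the clinical evaluation; a candidate above these limits may be re-screened once pressure is controlled.*

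Treated candidates keep the waiver of the lower limits and gain the upper ones. Untreated candidates face the same limits as now on the plain reading. The rewording makes explicit that an untreated person at, say, 150/75 mmHg is not admitted, so the sponsor should confirm that this is intended.

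The cost is one reworded criterion and one added sentence. Office pressure is already measured at the clinical evaluation, so no procedure is added apart from any re-screening. The downside is that a few treated candidates are refused or deferred. If the sponsor does want treated people exempt from the ceiling, the protocol should say so and give the reason.
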